## Abstract

Non-progressive acquired brain injury can cause cognitive and behavioral damage. These disorders may hinder the driving abilities of affected individuals, increasing crash risk. Consequently, driving license regulations have required people who suffer from brain injury to be examined by an approved doctor for their driving license to remain valid. The decree of March 28, 2022 requires that approved doctors consider elements of patients’ multiprofessional evaluation, but mentions neither the on-road driving assessment nor the neuropsychological assessment. However, these assessments are an integral part of the good practice recommendations certified by the French National Authority for Health. Practitioners in rehabilitation centers are used to applying the main recommendations despite the lack of consensus about the methods and tools used. Given these new regulations and the wide variety of real-life practices, this multicenter study aims to investigate the accuracy of tools for driving skill evaluation to guide professional practices. The cross-sectional study will investigate the sensitivity and specificity of both neuropsychological tests and an on-road assessment grid (Test Ride for Investigating Practical fitness to drive), through concordance analysis between the opinions expressed by professionals and between tools. Then, a cohort study will propose longitudinal follow-up of the drivers at 6 and 12 months in order to determine the predictive performance of the various assessments in terms of road risk, and to explore the relevance of educational support on driving habits and behavior. In this context, the quality of the decision-making process for maintaining a driving license is a major issue in limiting the road risk. As part of the measures issued by the Interministerial Road Safety Committee in 2023 aimed at “better detecting, assessing and monitoring unfitness to drive”, this study presents a challenge in terms of supporting public policies. It aims to harmonize the multiprofessional evaluation recently made mandatory, in order to better inform the approved doctor’s opinion.

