#### On-road driving assessment (RDA)

1.3.2

Complementary to the neuropsychological assessment, the RDA is considered as the “gold standard” in multiprofessional evaluation. The ecological nature of the on-road situation provides an opportunity to assess patients’ actual driving ability, enabling the adoption of compensatory strategies in the event of cognitive sequelae.

According to Michon’s hierarchical model, driving activity calls for three levels of skills and control, whose involvement varies according to the driver’s mental workload and the time constraints of the situation (Michon, 1985). The operational level involves a high time constraint (in the order of milliseconds) and a low cognitive workload, as it involves automatic action patterns. This level provides vehicle control, requiring quick and undemanding actions from the driver, such as manipulating the car controls or positioning the vehicle in the traffic lane. The intermediate tactical level involves a slightly lower time constraint during driving (in seconds) but calls on slightly higher-level cognitive processing systems, enabling the vehicle to be maneuvered in its environment. It is involved in situations requiring the driver to implement coping strategies that take into account both the perceived environment and the driver’s own driving goals (e.g., slowing down in heavy traffic or when visibility is poor). Finally, the strategic level involves a very low time constraint (in the order of minutes or even hours) but calls on very high-level cognitive functions, mainly upstream of the driving situation. In particular, it involves advance planning (before driving) and decision-making by the driver according to both external conditions (e.g., weather, traffic conditions) and the driver’s internal dispositions (e.g., fatigue, mood, and self-assurance). For example, the driver may choose to postpone departure to avoid traffic jams.

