##### Main criterion: concordance between professional assessments

2.3.1.1

To meet the main objective, the concordance of the results of the neuropsychological assessment, RDA and multiprofessional evaluation will be studied in pairs (agreement between professional assessments). Each professional involved in the study will give a “favorable,” “reserved” or “unfavorable” opinion based on their practice. Evaluation criteria will correspond to cross-tabulated numerical values of results from each assessment tool studied (neuropsychological assessment, RDA and multiprofessional evaluation). “Reserved” opinions indicating driving restrictions will initially be classified as “unfavorable,” so that the results can be expressed as a binary Favorable/Unfavorable variable for each assessment. The RDA results will also include the number of driving instructor interventions on pedals, steering wheel and other car controls, using categorical variables. The values *a*, *b*, *c* and *d* (Table 1) will be used to perform the concordance test detailed in the next section (“Statistical analysis”).

**Table 1 tab1:** Evaluation criterion of the main objective for contingency table.

		Assessment x_i_	
		Favorable	Unfavorable
Assessment x_ii_	Favorable	*a*	*b*
	Unfavorable	*c*	*d*

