#### Statistical analysis

2.3.3

To meet the main and secondary A and B objectives, concordance tests will be used to verify that two independent abilities to resume driving measures (two tests) of the same modality—“Favorable” or “Unfavorable”—are equal. Concordance analyses between tests (binary variables) will be expressed in the form of concordance percentages, simple kappa coefficient and its 95% confidence interval. Analyses between TRIP (continuous variable) and other tests (binary variables) will be conducted using *t*-tests or Mann–Whitney tests depending on the TRIP score distribution. Multivariate regression will also be used to study measures’ concordance and prediction levels, for both objectives. It will be logistic or linear, depending on the studied variable (i.e., approved doctor’s opinion for objective A and TRIP results for objective B).

A sensitivity and specificity analysis of the approved doctor’s opinion will also be carried out. Performance metrics (Secondary Objective C) will be calculated from the confusion matrix values (Table 4):$$\mathrm{Accuracy:}\frac{RP+RN}{RP+RN+FP+FN}$$$$\mathrm{Sensitivity (Se):}\frac{RP}{RP+FN\text{.}}$$$$\mathrm{Specificity (Sp):}\frac{RN}{FP+RN}$$$$\mathrm{Positive predictive value (PPV) or Precision (Pr):}\frac{RP}{RP+FP}$$$$\mathrm{Negative predictive value (NPV):}\frac{RN}{FN+RN}$$

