#### Relevance of on-road assessment

3.1.2

- In the event of concordance between opinion following RDA and other assessments (neuropsychological, multiprofessional, approved doctor’s opinion), the assessment tools mentioned can be considered to be good predictors of driving ability, in accordance with the literature (Marshall et al., 2007).- In the event of a discrepancy between RDA and other assessments, the RDA value will remain undeniable, but results can be explored and discussed depending on which assessment there is a discrepancy with, and the direction of this discrepancy. More specifically, a discrepancy between RDA and neuropsychological assessment can highlight coping strategies linked to awareness of cognitive disorders. In fact, correlation between neuropsychological assessment and actual driving may depend on the individual’s level of awareness of their abilities (Griffen et al., 2011). These results would not, therefore, call into question value of the RDA. On the other hand, a discrepancy between the opinion given following RDA and that given by the PRM doctor (multiprofessional evaluation) or the approved doctor may raise questions about value of the RDA, or at least the importance attached to it by doctors (PRM or approved doctor).- In the event of concordance between the TRIP score and the various assessments, TRIP can be considered a relevant tool for predicting driving ability. Conversely, in the event of discrepancies between TRIP and other assessments, the usefulness of this grid can be discussed. Further analysis could highlight the relevance of certain sub-scores.- In the event of concordance between the number of interventions on the controls and professional opinions, this criterion can then be considered to be a good predictor of driving ability. On the other hand, in the event of discrepancies, a certain tolerance may be accepted if the driving instructor intervenes on the controls during RDA.

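### Sensitivity and specificity are promised through concordance analysis, but percent agreement and simple kappa with no named reference give neither these quantities nor the direction of discrepancy

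*Protocol article*

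**What the plan says.** The Abstract sets the cross-sectional aim as accuracy: "The cross-sectional study will investigate the sensitivity and specificity of both neuropsychological tests and an on-road assessment grid", the grid being TRIP. The route is given in the same sentence: "through concordance analysis between the opinions expressed by professionals and between tools".

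Section 2.3.1.1 defines the main criterion: "the concordance of the results of the neuropsychological assessment, RDA and multiprofessional evaluation will be studied in pairs". Opinions are made binary, with reserved initially counted as unfavorable. Cells a to d of Table 1 "will be used to perform the concordance test detailed in the next section". Tables 2 and 3 use the same layout for objectives A (approved doctor's opinion) and B (TRIP grid).

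Section 2.3.3 describes the purpose as follows: "concordance tests will be used to verify that two independent abilities to resume driving measures (two tests) of the same modality" are equal. Results for binary pairs "will be expressed in the form of concordance percentages, simple kappa coefficient and its 95% confidence interval".

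Two further places bear on this. In section 1.3.2 "the RDA is considered as the" gold standard of the multiprofessional evaluation. In section 3.1.2, discrepancies between the RDA and other assessments are to be discussed "depending on which assessment there is a discrepancy with, and the direction of this discrepancy".

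**The concern.** Sensitivity and specificity need one assessment to be designated as the reference. Percent agreement and kappa treat the two assessments alike and need none. The background calls the RDA the gold standard, but the analysis sections never make the RDA opinion the reference for a cross-sectional pair. The method named in the abstract therefore cannot produce the quantity named in the abstract.

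Two kinds of disagreement have different meanings here. A tool that passes drivers whom the road test fails is a safety problem. A tool that fails drivers whom the road test passes may be picking up the compensating drivers described in section 2.4. Percent agreement and kappa merge the two.

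The stakes lie in how the results will be read. Section 3.1.1 turns concordance into a good predictor, and discrepancy into a tool that cannot be considered reliable. Sections 3.4.1 and 3.4.2 carry the conclusions on to professional practice and the training of approved doctors.

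**Working it through.** The article gives no kappa, agreement, sensitivity, specificity or favorable rate, so there is no figure of its own to reproduce. The tables below are illustrations. Only n = 100 (section 2.1) and the cell layout (Table 1) come from the document.

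**Formulas.** Rows are the index assessment (for example the neuropsychological opinion), columns the reference (for example the RDA opinion), and positive means unfavorable.
- Agreement po = (a+d)/n
- Chance agreement pe = [(a+b)(a+c) + (c+d)(b+d)]/n²
- Kappa = (po − pe)/(1 − pe)
- Sensitivity = d/(b+d); specificity = a/(a+c)
- Difference in favorable rates, rows minus columns = (b − c)/n

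**1. Direction.** Swapping b and c leaves po and pe unchanged. In both tables below, po = 80/100 = 0.80, pe = 0.80 × 0.60 + 0.20 × 0.40 = 0.56, and kappa = 0.24/0.44 = 0.545 (large-sample 95% CI 0.39 to 0.70).

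| (a,b,c,d) | Agreement | Kappa | Sensitivity | Specificity | (b − c)/n |
|---|---|---|---|---|---|
| (60,20,0,20) | 80% | 0.545 | 20/40 = 50% | 60/60 = 100% | +20 points |
| (60,0,20,20) | 80% | 0.545 | 20/20 = 100% | 60/80 = 75% | −20 points |

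In the first table the index assessment passes half of those whom the reference fails. In the second it passes none of them but fails a quarter of those whom the reference passes. Exact McNemar gives p = 2 × 0.5^20 ≈ 0.000002 in both, and the sign of b − c shows which way the disagreement runs.

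**2. Dependence on the favorable rate.** At a fixed 90% agreement:
- (45,5,5,45): pe = 0.50, kappa = 0.40/0.50 = 0.80
- (85,5,5,5): pe = 0.81 + 0.01 = 0.82, kappa = 0.08/0.18 = 0.44

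Agreement by category shows why. On unfavorable it is 2d/(2d+b+c), that is 90/100 = 0.90 and 10/20 = 0.50. On favorable it is 2a/(2a+b+c), that is 90/100 = 0.90 and 170/180 = 0.94.

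With sensitivity and specificity both held at 0.85, kappa is 0.70, 0.66, 0.60, 0.46 and 0.31 when the unfavorable share is 50, 30, 20, 10 and 5%, while agreement stays at 85%. With sensitivity 0.80 and specificity 0.90, kappa is 0.70 at 50%, 0.71 at 40% and 0.39 at 5%, while agreement rises from 85% to 89.5%. So the fall belongs to kappa alone, and mainly to lopsided splits.

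**3. Do the other planned analyses supply the promised quantity?**
- Correlations of raw neuropsychological scores with TRIP (2.3.1.2.2): association, not sensitivity or specificity.
- t-tests or Mann–Whitney tests of continuous TRIP by binary opinion (2.3.3): a comparison of groups.
- Logistic or linear regression (2.3.3): the outcomes named are the approved doctor's opinion and TRIP results, not the RDA opinion.
- Sensitivity and specificity of the approved doctor's opinion (2.3.3): concerns another assessment, with no reference stated.
- Objective C metrics (2.3.2.1, Table 4): full sensitivity, specificity and predictive values, but against road risk perceived by participants at 6 and 12 months, so not cross-sectional.

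**The case against.** The strongest reply is that the main criterion is concordance, for which percent agreement with kappa is conventional, that the study declares itself exploratory, and that section 2.1 places the full protocol on OSF. Much of this stands for the choice of extra statistics. It does not remove the mismatch. The article has its own statistical section, which names the statistics for these pairs, prints sensitivity and specificity formulas, and assigns those formulas to objective C.

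A reader might infer more than the document supports:
- *That only agreement and kappa are planned.* Not so; step 3 of the working lists five other analyses. They fall short of the promised quantity, but they exist.
- *That on-road performance is never the criterion.* TRIP is the grid scored after the RDA, and neuropsychological scores are correlated with it to find the most predictive tools. Only the binary RDA opinion lacks a reference role.
- *That kappa will be tested against zero.* No such null is stated. What can be faulted is the wording that concordance tests verify equality, which a kappa with its interval does not do.
- *That both summaries fall with prevalence.* Only kappa does. Percent agreement is reported beside it, so a reader could notice the divergence.
- *That direction is ignored.* Tables 1 to 3 separate b and c, section 2.4 states directional expectations, and section 3.1.2 is discussion text rather than a promise of a test. It is the two summary statistics that lose direction.

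**Conclusion.** The point holds in a limited form. For the cross-sectional binary pairs, the planned summaries cannot yield the sensitivity and specificity that the abstract promises, nor the direction that section 3.1.2 means to interpret. No other planned analysis supplies them.

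The size is shown by illustration: identical agreement (80%) and kappa (0.545) are compatible with sensitivity/specificity of 50%/100% or 100%/75%. The symmetry result needs no assumption about the data. The effect of lopsided margins rests on an assumed favorable rate, since none is given, and counting reserved opinions as unfavorable will itself shift that rate.

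The data to be collected are not at fault and the quantities can be recovered from the planned tables, so this should be corrected before analysis but does not undermine the design. It does not support a claim that the cross-sectional part is uninformative about which tests relate to on-road driving: the TRIP correlations and regression address that.

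**What to change.** 1. In section 2.3.3, name the RDA opinion as reference for the neuropsychological opinion. Report sensitivity and specificity with 95% confidence intervals (Wilson), and the ROC AUC of each neuropsychological score against the RDA opinion.
2. For every pair, report cells b and c, the paired difference in favorable rates with exact McNemar, and positive and negative agreement beside kappa.
3. Replace the wording that concordance tests verify equality with a statement that agreement will be estimated.
4. State the reference for the sensitivity and specificity analysis of the approved doctor's opinion.
5. Amend the abstract so that it does not promise cross-sectional sensitivity and specificity for TRIP. Under section 2.2.1.4 the professionals in the car complete TRIP jointly and also issue the RDA opinion, so such figures would partly measure raters agreeing with themselves.

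The cost is a few table rows, some rewording and a narrower stated aim for TRIP; no new data are needed. Precision will be modest and the intervals will show it. If 10, 20 or 50 participants were unfavorable on the RDA (assumed counts), an observed sensitivity of 80% would have a Wilson interval of 49% to 94%, 58% to 92% or 67% to 89%.

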## Introduction

1

### Brain injury and accident rates

1.1

Non-Progressive Acquired Brain Injury (npABI) affects almost 300,000 people in France every year. This term covers traumatic brain injury (TBI), stroke, cerebral anoxia, encephalitis and meningoencephalitis. These injuries can cause cognitive-behavioral and sensory-motor disorders that can restrict people’s independence, and particularly their fitness to drive, since a reduced ability to react to maintain vehicle control compromises safe driving. Cognitive-behavioral disorders thus lead to an increase in road accidents and a 2.3-fold higher road risk among people with npABI (Formisano et al., 2005). This increased risk of accident for people with npABI is observed in the short (6 months), medium (3 years) and long (10 years) term since injury (Bellagamba et al., 2020; Lundqvist et al., 2008). However, many factors influence this risk, including age, education level, time since injury, extent of injury, nature of cognitive impairments and number of years licensed. This significant inter-individual variability calls for a singular evaluation of the ability to resume driving (Bellagamba et al., 2020; Novack et al., 2010). In this context, the quality of the decision-making process for maintaining the driving license of people with npABI is a key factor in limiting road risk.

### Regulatory framework

1.2

In order to guarantee road safety for people with npABI (as well as for other road users), regulations govern their return to driving. Since 2005, “driving license holders suffering from a medical condition incompatible with […] the maintenance of their driving license are subjected to a medical examination of their fitness to drive […].” These people must apply to a doctor approved by the prefect, who will issue an opinion on their fitness to drive. The decree of March 28, 2022 listing the medical conditions incompatible with driving requires that the approved doctor’s opinion take into account the evaluation carried out by a multidisciplinary team consisting of at least a specialist (neurologist or Physical and Rehabilitation Medicine specialist—PRM) and an occupational therapist (Légifrance, 2022). The approved doctor can also ask for an on-road driving test if he considers that a real-life situation is necessary. The publication of this decree was a major step towards taking better account of the issue of resuming driving following a npABI. Nevertheless, its application raises many questions about the practice of the professionals concerned:The decree does not mention the assessment of the invisible impairments of npABI (neuropsychological assessment)The decree does not specify the conditions under which the approved doctor should request an on-road driving assessmentInterpretation of the multiprofessional evaluation by approved doctors often varies, probably for several reasons (e.g., lack of pathology-specific training to obtain approval, diversity of practices and thus of level of expertise concerning npABI)

### The multiprofessional evaluation

1.3

An expert group issued good practice recommendations concerning the driving ability evaluation after npABI, which were certified in 2016 by the French National Authority for Health (Haute Autorité de Santé, HAS). These recommendations aim to standardize the decision-making process of the driving ability evaluation (Haute Autorité de Santé, 2016). This guide helps to identify, assess and support people with npABI who wish to resume driving. According to these recommendations, a multiprofessional evaluation should be carried out prior to any resumption (12th recommendation). Assessments are based on (a) visual functions, with ophthalmological evaluation recommended in the event of any doubt about an alteration of the visual pathway, (b) sensory-motor functions, with an on-Road Driving Assessment (RDA) recommended in the event of sensory-motor sequelae, and (c) cognitive functions, with the recommendation to carry out an RDA in cases of cognitive-behavioral sequelae. In practice, this multiprofessional evaluation takes place in a rehabilitation center, and should include an occupational therapy assessment, a neuropsychological assessment and an RDA with a driving instructor and a therapist. The PRM doctor integrates the medical component of this multiprofessional evaluation (requesting additional tests if necessary) and submits an advisory opinion to the approved doctor on the person’s ability to resume driving. The present field research focuses on studying the performance of the neuropsychological assessment and on-road assessment, integrated into the multiprofessional evaluation, with a view to harmonizing and improving practices.

#### Neuropsychological assessment

1.3.1

Driving is a complex activity involving perceptive-cognitive, metacognitive and social-cognitive functions (Groeger, 2015), supported by a large cerebral network at both cortical and subcortical levels. A npABI, whatever its location and origin, may affect a driver’s mental functions, making their driving less safe for themselves and other road users. As cognitive-behavioral disorders represent a higher road risk factor (Formisano et al., 2005; Bellagamba et al., 2020; Lundqvist et al., 2008; Bivona et al., 2012), an overall neuropsychological assessment is essential to assess the efficiency of the mental functions required in a driving situation. When assessing driving ability, neuropsychologists focus mainly on attentional functions. Attentional processes enable the driver to simultaneously and rapidly process different types of information (traffic signals, vehicles, pedestrians, bicycles, etc.) of varying intensity (depending on traffic conditions, for example), often over a prolonged period of time. Sawada et al. (2019) model defines attention as a multidimensional concept, distinguishing between intensive (phasic alertness and sustained attention) and selective (selective attention and divided attention) aspects, which operate under the control of a supervisory attentional system (SAS) enabling the optimal management of attentional resources in a given situation. These attentional resources are limited (Kahneman, 1973) and particularly vulnerable to the effects of brain damage. This vulnerability undoubtedly stems from the fact that the attentional system is supported by widely distributed brain networks: fronto-parietal, pulvinar, insula… (Azouvi et al., 2017; Mathias and Wheaton, 2007). Aberrant driving behavior, which is more frequent in people with npABI, is mostly attributable to inattention errors (Bellagamba et al., 2020) and attentional test results are therefore predictive of driving ability (Mathias and Lucas, 2009). For example, spatial attention disorders, such as unilateral spatial neglect, are often considered as a reason for being unfit to drive (Akinwuntan et al., 2003) and merit a systematic investigation.

Neuropsychological assessment also targets executive functions, involved in complex situations when routine actions are no longer sufficient (e.g., reacting to an unexpected event, changing route, managing speed in traffic). Diamond (2013) takes an integrative approach to modeling the executive system, distinguishing three basic functions (working memory, inhibition, and flexibility), to which are attached three higher-level functions (reasoning, problem-solving, and planning). The executive system is supported by a widely distributed anteroposterior network in which the prefrontal cortex, which is particularly vulnerable in TBI (frontal impact), plays an essential role. As driving is a complex activity during which routines are rarely sufficient, an executive dysfunction can then be considered as a predictor of underperformance during a driving assessment (Motta et al., 2014).

The neuropsychological assessment often focuses on memory abilities. Anterograde memory (the ability to acquire new information) is a fairly controversial predictor of driving ability in the literature (Wolfe and Lehockey, 2016). However, working memory (processing and temporary retention of information required to carry out activities) is particularly involved in controlled activities such as driving, when it comes to following a route or driving in heavy traffic (e.g., Aksan et al., 2015). Barrouillet and Camos recently proposed a two-system modeling of working memory based on the TBRS (Time-Based-Resource-Sharing) cognitive model (Camos and Barrouillet, 2014). The peripheral system is composed of a declarative module providing access to information stored in long-term memory, a goal module and sensory buffers (motor, phonological, and visuo-spatial). The central system processes and maintains memory traces (from the peripheral system) in an episodic buffer. Attention plays a central role in this model, as processing and storage compete for a single, limited attentional resource that must be shared between the two components. Two fMRI (functional magnetic resonance imaging) meta-analyses have confirmed the activation of the dorsolateral prefrontal cortex and posterior parietal cortex during working memory tasks (Owen et al., 2005; Rottschy et al., 2012). As these areas are vulnerable to brain damage, a working memory disorder may impair a patient’s ability to drive. In fact, several studies have shown that good working memory skills are associated with better driving performance, such as lane changing (Ross et al., 2014; Zhang et al., 2023), concentration levels (Zhang et al., 2023) or compliance with the highway code in double-tasking situations (Broadbent et al., 2023).

Although little has been documented in the literature, a psycho-behavioral assessment enables clinicians to make hypotheses about possible behavioral disorders at the root of risky behavior. Behavioral disorders linked to a lack of control (impulsivity, road rage, urgency behaviors, etc.) are frequently observed following brain injury (Billieux et al., 2014; Rochat et al., 2010), and can lead to inappropriate decisions, actions and reactions likely to increase road risk. Social cognition refers to “the ability to construct representations about the relationships between oneself and others, and to use these representations flexibly to guide one’s social behavior” (Adolphs, 2001). It requires cognitive and affective theory of mind, enabling individuals to infer others’ mental states in order to react appropriately in a shared environment, such as a road situation. Investigating social cognition thus makes it possible to understand a driver’s ability to adapt their own behavior to that of other road users. Finally, self-awareness sheds light on the development of behavioral self-regulation mechanisms, in that subjective feelings are a good predictor of self-regulation (Ang et al., 2019). Thanks to drivers’ awareness of their own abilities, they will be able to adapt their driving behavior to make it safe despite any deficits they may have (e.g., breaks in the case of asthenia, speed reduction in the case of psychomotor slowing, avoidance of rush hours in the case of sustained attention disabilities). A study has shown that self-awareness of deficits correlates with driving ability in real-life situations (Griffen et al., 2011).

